***Procedure:*** Potential participants will undergo a two-step screening process. The first step will be conducted via telephone interview, using an eligibility checklist. Potentially eligible women will then be invited to an in-person screening session on the first day of their next menstrual period. During this session, women will complete the screening questionnaire and IPAQ to determine eligibility, assess baseline physical-activity levels, and obtain written informed consent and anthropometric measurements. Baseline assessments of primary and secondary outcomes and the costs and absenteeism data associated with each individual’s previous three menstrual cycles will be performed, and saliva samples will be collected. Participants will then be randomised into HIAT or WLC groups. Participants in the HIAT group will receive supervised treadmill training for the first 12 weeks of the trial. To minimise carryover effects, a four-week washout period will be observed for all study participants before cross-over. During the washout period, the HIAT group will discontinue exercise, and both groups will continue to manage pain as usual (i.e. with analgesics). After the four-week washout period, the cross-over period will begin during Week 16, and the participants initially randomised to the WLC group will receive the HIAT regimen from Weeks 14–28. Participants initially randomized to HIAT group will be instructed not to engage in exercise during the remainder of the study period (i.e. Weeks 14-28). Participants will be permitted to use analgesics for menstrual pain as needed throughout the study and will be instructed to record the dose and number of pills consumed in an electronic diary. As a diagnosis of primary dysmenorrhea can be confirmed by collecting detailed history;^33, 34^ a pelvic examination/ ultrasound will not be conducted.

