*Economic evaluation*. We will analyse the results of HIAT versus WLC over a 12-week, within-trial period (i.e., at T2).^28^ The cost-effectiveness for the entire 28-week time horizon will also be explored through T3 data observed in the HIAT arm and extrapolation of WLC data.^28^ The primary analysis will be conducted from a societal perspective (short-term direct costs, intervention costs, costs unrelated to the intervention [healthcare services and medication costs] and indirect costs, such as absence from work and impact on productivity due to primary dysmenorrhea).^48^ The secondary analysis will be conducted from a healthcare perspective (direct costs, including intervention costs and costs of other care, *excluding* absenteeism costs).^48^ Cost and absenteeism data that are collected at baseline (i.e., previous three menstrual cycles) will be used as predictors of future costs in the analysis. The EQ-5D-3L will be used to determine the QoL for the HIAT and WLC groups. The cost per participant will be calculated by multiplying unit costs identified from the HK government standardised national price list and resource quantities.^28^

An electronic diary (<https://forms.gle/gvoLHAoDqySQFr4GA>) will be used to record cost expenditures and work absenteeism. All participants will be provided with access to the cost diary, post-randomisation. Participants with limited access to the internet will be provided with printed hard copies of the cost and absenteeism diary, along with stamped and addressed return envelopes. Participants will be instructed to complete the diary during the week of menstruation each month. The research team members will be able to access the electronic diary to obtain a summary of the completed items for all study participants. The student assistant will contact participants by telephone for incomplete entries, to acquire additional details, or for failure to complete the diary.

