***Hypothesis 2.*** The mediation effects of increased progesterone levels on pain will be assessed using the Sobel test.^51^ A four-step model using linear regression will be tested. In Step 1, the regression coefficient between prostaglandin levels and pain (Path C) will be estimated. In Step 2, the regression coefficient between progesterone and prostaglandin levels (Path A) will be estimated. In Step 3, the regression coefficient between pain and prostaglandin levels, along with the mediator, progesterone levels (Path B), will be evaluated. Step 4: the Sobel test will be used to estimate the standard error of Path AB using the formula B^2^SA^2^ + A^2^SB^2^, where A and B are the regression coefficients of Paths A and B, respectively, and SA and SB are the standard errors of Paths A and B, respectively.^51^ The online Sobel test calculator (<http://quantpsy.org/sobel/sobel.htm>) will be used. Hypothesis 2 will be supported if the Sobel test indicates a significant (p < 0.05) mediation effect.

***Hypothesis 3***. The unadjusted mean costs and cost differences between HIAT and the usual care groups for total and disaggregated costs (intervention costs, healthcare utilisation costs, including healthcare services and medications utilised, and absenteeism costs) will be calculated.^48^ The seemingly unrelated regression (SUR) analyses will be used to estimate the total cost differences (ΔC) and effect differences (ΔE). The SUR analyses will be performed by adjusting for baseline demographic and health characteristics (such as pain intensity and menstrual-cycle length or the number of bleeding days) between groups.^48, 52^ The advantage of SUR is that two regression equations, one for ΔC and one for ΔE, are modelled simultaneously allowing possible correlations between cost and outcome differences to be accounted for.^48, 53^

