The EQ-5D responses will be converted into utility scores to estimate the gain or loss of quality-adjusted life-years (QUALYs). The incremental cost-effectiveness ratio (ICER) will be calculated using the formula ICER = ΔC / ΔE. The advantage of this approach is that our confidence intervals do not rely on the usual normality assumption. Uncertainty surrounding the ICERs and the 95% confidence intervals around cost differences will be estimated using bias-corrected and accelerated bootstrapping with 5,000 replications.^48^ The cost-effectiveness of the intervention groups will be geographically represented using the cost-effectiveness plane (CE). The threshold (λ) for cost-effectiveness or the amount of money the country is willing to pay to gain one unit of effect (QALY) will be calculated.

Further, we will determine whether the intervention is cost-effective by utilising two other thresholds to test the robustness of our conclusion: (1) GDP per capita (in terms of purchasing-power parity), which is the threshold suggested by the World Health Organisation Commission for Macroeconomics and Health for an intervention to be ‘very cost-effective’;^54^ and (2) the country-specific thresholds published by Woods et al.,^55^ based on extrapolating the opportunity costs of healthcare spending in the United Kingdom. The cost-effectiveness acceptability curve (CEAC) will be derived based on the λ value. Using the CEAC, the cost-effective treatment options will be predicted based on the different λ levels. A secondary analysis will be performed from a healthcare perspective by excluding absenteeism costs.^48^ The robustness of the primary analysis will be tested using the following two sensitivity analyses: (1) repetition of the analysis including completed participants alone; and (2) excluding cost-outliers or data from participants with extremely high absenteeism costs.^48^ Hypothesis 3 will be supported if HIAT yields cost (direct and indirect) savings and results in lower healthcare utility compared with WLC receiving usual care at assessment T2.

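### Baseline EQ-5D utility is not named as a covariate for the QALY difference, and EQ-5D-3L is not explicitly placed at T1

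*Protocol*

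**What the plan says.** The covariates for the economic analysis are described in two places.

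- Statistical tests and anticipated results, Hypothesis 3: "The SUR analyses will be performed by adjusting for baseline demographic and health characteristics (such as pain intensity and menstrual-cycle length" or bleeding days). The list is introduced as examples, and the choice between cycle length and bleeding days is left open. Baseline cost and absenteeism are not mentioned.
- Economic evaluation: cost and absenteeism data from the three menstrual cycles before baseline "will be used as predictors of future costs in the analysis". This concerns costs only.

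On the effect side, "The EQ-5D-3L will be used to determine the QoL for the HIAT and WLC groups", with no assessment times given. Hypothesis 3 then says: "The EQ-5D responses will be converted into utility scores to estimate the gain or loss of quality-adjusted life-years". No formula follows. The main horizon is T2: "We will analyse the results of HIAT versus WLC over a 12-week, within-trial period".

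On timing, Research design and recruitment mentions economic evaluations only at 12 weeks. The Procedure section lists "Baseline assessments of primary and secondary outcomes and the costs and absenteeism data" for the three previous cycles, without naming EQ-5D.

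**The concern.** The QALY is the unit of effect in the ICER, and the best single predictor of a participant's QALYs over 12 weeks is likely to be her utility at the start. When QALYs are computed as the area under the utility curve, the baseline value is itself half of the quantity analysed. A chance difference between arms at T1 then counts as effect unless the model removes it. Over so short a horizon QALY differences are small in absolute terms, so a small imbalance can matter to a ratio with that difference in its denominator.

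There is also a practical risk. A covariate list can be completed later in an analysis plan, but a baseline utility that was never collected cannot be recovered. The protocol does not rule out EQ-5D at T1, but nowhere says plainly that it is taken then.

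**Working it through.** The protocol gives no utility SD, no T1–T2 correlation and no expected QALY difference, so it has no figure of its own to reproduce here. The calculation compares the standard error (SE) of the between-arm QALY difference without and with baseline utility in the model.

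**Inputs from the protocol:** horizon 12 weeks (12/52 = 0.231 year); 65 per arm enrolled, with 50 per arm as the Hypothesis 2 requirement before dropout; baseline pain named as a SUR covariate.

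**Assumptions:** equal utility SDs at T1 and T2; T1–T2 utility correlation r from 0.3 to 0.7; baseline pain correlates c (in absolute value) with baseline utility, and with T2 utility only through baseline utility.

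**Variance ratios (without baseline utility / with it):**

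- Area under the curve, QALY proportional to (U1 + U2)/2: 0.5(1 + r) / [0.25(1 − r²)] = 2/(1 − r).
- The same, with pain already adjusted: 1 + (1 + r)(1 − c²)/(1 − r).
- Change from baseline: 2/(1 + r).
- T2 utility only: 1/(1 − r²).

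**SE ratios (square roots of the above):**

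| r | Area under curve | with pain, c = 0.4 | with pain, c = 0.6 | Change from baseline | T2 only |
|---|---|---|---|---|---|
| 0.3 | 1.69 | 1.60 | 1.48 | 1.24 | 1.05 |
| 0.5 | 2.00 | 1.88 | 1.71 | 1.15 | 1.15 |
| 0.7 | 2.58 | 2.40 | 2.15 | 1.08 | 1.40 |

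Example at r = 0.5, area under the curve: 2/(1 − 0.5) = 4.0, square root 2.00. A simulation with 65 per arm at the same r gave 1.97. The ratio does not depend on sample size, apart from a small loss of degrees of freedom. All ratios exceed 1, so baseline utility gains precision under each formula tried.

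**Imbalance in QALY units (area under the curve).** With an assumed utility SD of 0.1–0.2, the SE of the chance baseline difference is SD × √(2/n):

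- SD 0.1, 65 per arm: 0.1 × √(2/65) = 0.018
- SD 0.2, 50 per arm: 0.2 × √(2/50) = 0.040

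The direct baseline half carries 0.5 × 12/52 = 0.115 of this into the QALY difference, about 0.002 to 0.005 QALY. A baseline difference of 0.03, unremarkable on those SEs, contributes 0.03/2 × 12/52 = 0.0035 QALY. A true treatment effect of 0.03 on T2 utility would contribute the same amount.

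**The case against.** The strongest reply is that the Hypothesis 3 covariate list is open. Baseline EQ-5D utility is a baseline health characteristic and may be meant, and a full list by equation is ordinary analysis-plan content. That stands as far as it goes: a reader might infer that baseline utility is excluded, but the text supports only that it is not named.

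A reader might also infer that the two covariate statements contradict each other. They do not have to. One names predictors of cost, the other gives examples for the SUR model, and both can hold together. They need aligning. For the same reason the precision to be gained from baseline cost is already promised under Economic evaluation and is not a shortfall of the plan.

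On timing, EQ-5D sits in a paragraph that follows the secondary outcomes, and those are assessed at baseline. Collection at T1 is therefore a fair reading, and speaking of a gain or loss in QALYs fits it. It remains an inference.

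Finally, bootstrapping is planned for ICER uncertainty. It will reflect the wider uncertainty but will not recover the lost precision.

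What survives is narrow: the protocol commits to baseline adjustment and gives examples, yet leaves out the one most closely tied to the effect measure, and does not secure its collection.

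**Conclusion.** The point holds as a matter of precision and of securing data. If the named covariates are used as written, the SE of the QALY difference is larger than it need be: about 1.7–2.6 times for area-under-curve QALYs, 1.5–2.4 times once baseline pain is adjusted with c of 0.4–0.6, and about 1.05–1.4 times if the effect is change from baseline or T2 utility alone. All of this rests on assumed correlations of 0.3–0.7, equal SDs and a QALY formula that the protocol does not give.

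Two stronger readings are not supported. One is that the SE is simply doubled: that value belongs to area-under-curve QALYs at r = 0.5 with no help from other covariates, and it is neither a general figure nor a ceiling. The other is that the economic conclusion is biased or would reverse. Under randomisation the imbalance is chance error, and the protocol gives no expected QALY difference against which 0.0035 could be judged.

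The outputs affected are the QALY difference, the ICER, the cost-effectiveness plane and the acceptability curve. The stated rule for supporting Hypothesis 3 turns on cost savings and, as it reads in context, lower healthcare use at T2, so it is not touched.

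**What to change.** In the Hypothesis 3 paragraph, keep the planned covariates and specify the additions by equation:

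- Effect equation: add baseline EQ-5D utility.
- Cost equation: carry over baseline cost and absenteeism, as Economic evaluation already promises.

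In Research design and recruitment and in Procedure, state that EQ-5D-3L is completed at T1.

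The cost is a few lines of analysis wording and, if EQ-5D is not already part of T1, a five-item form at a visit that takes place anyway.

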***Research design and recruitment.*** A mixed-methods study, including a cross-over RCT, and semi-structured focus groups, alongside economic evaluation, will be conducted. A Cross-over design will be adopted to minimize the effect of confounders and inter-individual variability (because each participant serves as their own control)^27^ and encourage participant enrolment in the trial.^28^ A mixed-methods approach will be considered because the combination of qualitative and quantitative methods can contribute to interdisciplinary and comprehensive research evidence.^29^ This trial will include: (1) a two-step screening phase for eligibility; (2) a baseline assessment (time-point [T1]); (3) 12 weeks of supervised treadmill training for the HIAT group; (4) post-treatment outcome assessments and economic evaluations at 12 weeks (T2); (5) a washout period for four weeks, followed by the cross-over of HIAT and WLC groups; (6) 12 weeks of supervised treadmill training for the WLC group; (7) outcome assessments at 28 weeks (T3); and (8) semi-structured focus groups at 32 weeks. Potential participants will be recruited via advertisements (study flyer) distributed at the Hong Kong Polytechnic University and the Education University of Hong Kong (please see upport letter) campuses and throughout the local community and by word-of-mouth.

***Sample size:*** G-Power analysis^30^ (3.1.9.2), set for an F-test (analysis of variance (ANOVA), was used to estimate the sample size required to reliably test the study hypotheses. We will enrol 130 participants (65 per group), allowing for a 30% attrition rate (the drop-out rate in our previous RCT^9^ with a seven-month follow-up was 20%–23%). For Hypothesis 1, the estimated sample size was 86 (43 per group). The power was set to 90%, the alpha level was 0.05, the drop-out rate was 30%, and effect-size was 0.60 (from our previous RCT^9^). For Hypothesis 2, based on estimated changes in progesterone levels from our pilot trial (***d*** = 0.36),^13^ the sample size required to detect differences in progesterone with 90% power at the 5% significance level is 100 (50 per group). Assuming a 30% drop-out rate, 130 participants (65 per group) would be required.

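### A BCa bootstrap interval on the ICER is unreliable when the QALY difference is not clearly separated from zero; net monetary benefit gives a usable interval from the same resamples (minor)

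*Protocol*

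**What the plan says.** Protocol, Statistical tests and anticipated results, Hypothesis 3: SUR models give ΔC and ΔE, and "The incremental cost-effectiveness ratio (ICER) will be calculated using the formula ICER = ΔC / ΔE". The next sentence reads "The advantage of this approach is that our confidence intervals do not rely on the usual normality assumption", followed by "Uncertainty surrounding the ICERs and the 95% confidence intervals around cost differences will be estimated using bias-corrected and accelerated bootstrapping with 5,000 replications". The same paragraphs plan a cost-effectiveness plane, an acceptability curve (CEAC), a threshold λ that is to be calculated, and two further thresholds: GDP per capita and a published country-specific value. Hypothesis 3 counts as supported on cost savings and lower healthcare utility at T2.

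Protocol, Economic evaluation: the main comparison is at 12 weeks ("We will analyse the results of HIAT versus WLC over a 12-week, within-trial period"), and the effect measure comes from the EQ-5D ("The EQ-5D-3L will be used to determine the QoL for the HIAT and WLC groups").

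No expected utility gain, utility SD, ΔE, ΔC or ICER is given. Net benefit is not mentioned. Nor is there a rule for reporting the ICER when ΔE may be zero or when ΔC and ΔE have opposite signs.

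**The concern.** A ratio behaves badly when its denominator can change sign. If some resampled ΔE values fall below zero, the resampled ratios jump between large positive and large negative values, and their order no longer runs from better to worse. BCa only chooses adjusted percentiles of that distribution, so it cannot restore a meaningful order.

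There is a second problem that needs no assumed figure. Hypotheses 1 and 3 anticipate less pain and lower cost. If both appear as ΔE > 0 and ΔC < 0, the ICER is negative. A negative ICER also arises when HIAT costs more and does harm.

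At stake is the readability of any error bar printed beside the ICER. The Hypothesis 3 conclusion is not at stake.

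**Working it through.** **Inputs from the protocol.** "We will enrol 130 participants (65 per group), allowing for a 30% attrition rate", so 65 per arm at enrolment and 65 × 0.70 = 45.5, about 45, after attrition. The method is BCa on ΔC/ΔE. The plan states no ICER, ΔE or interval figure that could be reproduced.

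**Assumed inputs (not in the protocol).** QALY effect d = ΔE/SD of 0.1, 0.2, 0.36 and 0.6. These are a range only: the protocol's 0.60 concerns Hypothesis 1 and its 0.36 concerns progesterone, and neither is a QALY effect.

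**Step 1: sign of the ICER.** Illustrative values:
- HIAT dominant: ΔC = -HK$500, ΔE = +0.005, so ICER = -500/0.005 = -100,000.
- HIAT dominated: ΔC = +HK$500, ΔE = -0.005, so ICER = 500/(-0.005) = -100,000. The value is identical.
- Same saving, doubled health gain: -500/0.010 = -50,000. The better result lies closer to zero.

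Net monetary benefit, NMB = λ × ΔE - ΔC, at an assumed λ of HK$200,000:
- dominant: 1,000 + 500 = +1,500
- dominated: -1,000 - 500 = -1,500
- doubled gain: 2,000 + 500 = +2,500

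NMB puts the three in the right order.

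**Step 2: what governs crossing zero.** Let z = d/√(2/n). If the observed effect equals d, the share of resamples with ΔE below zero is about Φ(-z). If the true effect equals d, the chance that the 95% interval for ΔE includes zero is about 1 - Φ(z - 1.96). Example: d = 0.2, n = 45: √(2/45) = 0.211, z = 0.95, Φ(-0.95) = 17%.

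The 12-week horizon does not enter. An assumed utility gain of 0.02 to 0.10, reached linearly, gives ½ × 12/52 × gain = 0.0023 to 0.0115 QALY, but the same factor scales the standard error, so z is essentially unchanged.

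**Step 3: coverage by simulation.** Set A: 600 trials per scenario with 1,500 resamples each; normal costs and effects; correlation -0.2; cost difference of -0.3, 0 or +0.5 SD; jackknife acceleration; no SUR adjustment. Set B: a separate simulation, also with normal data and assumed inputs. Paired values are n = 65 / n = 45, and coverage ranges in set A run over the cost scenarios.

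| d | Resamples with ΔE < 0 | 95% CI for ΔE includes 0 | BCa coverage, set A | BCa coverage, set B (45-65 per arm) |
|---|---|---|---|---|
| 0.1 | 28% / 32% | 92% / 93% | 62-77% / 59-76% | 56-66% |
| 0.2 | 13% / 17% | 79% / 84% | 76-84% / 73-83% | 73-79% |
| 0.36 | 2.0% / 4.4% | 46% / 60% | 91-94% / 87-90% | 86-92% |
| 0.6 | 0.03% / 0.2% | 7% / 19% | 95-97% / 95-97% | 95-96% |

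The bootstrap interval for net benefit at a fixed λ, from the same resamples, covered 93-96% in all 24 scenarios of set A (4 effects × 3 costs × 2 sample sizes) and 92-96% in set B. Monte Carlo error in set A is about 1-2 points.

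**Step 4: is d = 0.6 a safe assumption?** If QALYs are a two-point area under utility at T1 and T2, baseline utility adds noise but no effect. Then QALY d = utility d/√(2(1 + ρ)), where ρ is the correlation between T1 and T2. A T2 utility effect of 0.6 becomes 0.6/1.414 = 0.42 at ρ = 0 and 0.6/1.844 = 0.33 at an assumed ρ = 0.7. Adjusting for baseline utility would recover this. The protocol's example covariates do not name it, but the list is only illustrative.

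**The case against.** The strongest reply is that the protocol attaches 95% confidence intervals to cost differences only. For the ICER it speaks only of uncertainty, and it then plans a plane and a CEAC. Bootstrapped pairs shown on a plane are sound whatever the sign of ΔE, and a CEAC is already the share of resamples with positive net benefit at each λ. Reporting details may be left to a SAP, and Hypothesis 3 is not decided on an ICER interval.

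Most of this stands, and it is why the point is minor. What remains is that BCa is by construction an interval method, that the plan names it for the ICER, and that the sentence before refers to confidence intervals directly after the ICER formula. An ICER interval is the natural product of that text even though none is spelled out. The plan also intends to judge cost-effectiveness against thresholds, which is a net-benefit question, and it gives no interval for it.

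A reader might also infer that QALY differences over 12 weeks are so small that resamples must cross zero and coverage must be poor. The documents do not support that. No ΔE or SD is given, crossing depends on ΔE relative to its standard error, and at 0.6 SD coverage is nominal. Nor is it established that dominant and dominated resamples will mix. In set A the share of trials with more than 2.5% of resamples in each of those two quadrants ran from 1% to 75%, depending heavily on the assumed cost difference.

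**Conclusion.** The point holds in a conditional form and is minor. A BCa interval on ΔC/ΔE under-covers when ΔE is not clearly separated from zero: about 56-92% for assumed QALY effects of 0.1 to 0.36 SD with 45 to 65 per arm (set B; set A gives 59-94%), and near 95% at 0.6 SD. These figures rest on normal data, although real costs are usually skewed, and set A used no covariate adjustment, which would sharpen ΔE.

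The sign problem needs none of these assumptions: under cost savings with health gain the ICER is negative, and no interval on it can be read as better or worse.

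It would go too far to infer that the Hypothesis 3 conclusion or the economic evaluation as a whole is invalid. The plane and CEAC stand, and the Hypothesis 3 rule does not draw on an ICER interval.

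**What to change.** In the Hypothesis 3 paragraphs:

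1. Keep BCa for the cost differences, and state that no BCa interval will be reported for the ICER.
2. Give the ICER as a point estimate only when ΔC and ΔE have the same sign; otherwise state which option is dominant.
3. Report incremental net monetary benefit, λ × ΔE - ΔC, with its bootstrap 95% interval at each threshold the section names: the calculated λ, GDP per capita and the country-specific value.
4. Give the share of resamples in each quadrant beside the planned plane and CEAC.

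All of this comes from the same 5,000 SUR resamples. The cost is a change of wording in the protocol or SAP, with no new data, visits or participants.

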***Pilot trial***: We conducted a pilot trial to examine the effects of HIAT on plasma biomarkers that have been implicated in the pathophysiology of primary dysmenorrhea. The pilot trial findings indicated a trend towards increased progesterone levels (***d*** = 0.36) and decreased levels of prostaglandin F2 alpha (PGF2α) metabolites (***d*** = 0.35) in the HIAT group compared with those in the control group, which suggested that aerobic exercise may affect primary dysmenorrhea pain through effects on these mediators.^8, 13^

Because our research has supported the beneficial effects of HIAT, and a recent pilot study suggested a link between HIAT and progesterone and prostaglandin levels, the proposed randomised, controlled cross-over trial will test the following three hypotheses: (1) HIAT for 12 weeks will lead to significant reductions in pain intensity and absenteeism and improve academic performance compared to baseline levels; (2) pain improvements will be mediated by increased progesterone levels, resulting in decreased PGF2α levels; (3) HIAT will display superior cost-effectiveness compared with usual care (Wait-list control [WLC]) for primary dysmenorrhea treatment.

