***Intervention.*** The exercise intervention will last for 24 weeks (12 weeks for the HIAT group and 12 weeks for the WLC group) at PolyU. Supervised treadmill (Zebris FDM-T) training at PolyU will begin on the first day of the second menstrual period (baseline assessments will be completed during the first menstrual period). Exercise sessions at PolyU will be instructed and supervised by a registered physiotherapist (RPg student). Using this supervisory method, the participant-to-research person ratio will be 1:1. The rationale for providing supervised sessions is to increase adherence to study interventions because, in our previous RCT^9^, adherence was higher for supervised sessions than for unsupervised home exercise sessions. MHR will be calculated using the conventional age-predicted formula (220 – age). To achieve the target HR, the speed of the treadmill will be gradually increased, based on the participants’ HR, which will be displayed on the treadmill, and the rating of perceived exertion (RPE). Because the current proposed study does not involve graded, incremental exercise, graded-exercise testing (such as VO_2max_ evaluation) will not be performed.

*HIAT.* Women will perform treadmill-based aerobic exercise for three days a week, at 70%–85% of MHR for 30 minutes and perceived exertion of 14–16, based on the Borg RPE scale. This range^39^ is considered to represent HIAT. Aerobic training will be preceded by warm-up exercises for 10 minutes and followed by cool-down exercises for 10 minutes, at a perceived exertion of 11.0 (Borg RPE). These exercise parameters are based on our previous studies^9,10^ and the American College of Sports Medicine guidelines.^40^

*WLC*. Women in the WLC group will be instructed to continue with their usual activities and manage their pain as normal (i.e., with analgesics).

**Outcome measures: Primary outcomes:** *Pain intensity.* Average pain intensity during the last 24 hours during menstruation will be assessed using the 0–10 NRS,^41^ with 0 representing ‘No pain’ and 10 representing ‘Worst imaginable pain’.

*Absenteeism from university*: Access to a prospective electronic diary will be provided for each participant to record university absenteeism. Electronic diaries are reported as highly acceptable and feasible to use.^44^ Significantly increased compliance and accuracy have been reported with e-diary recording compared with traditional paper diaries.^44^

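### The success rule for Hypothesis 3 tests for cost savings and lower resource use, not cost-effectiveness, and can contradict the planned cost-utility analysis

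*Protocol*

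**What the plan says.** The hypothesis, at the end of *Background of Research*, is that "HIAT will display superior cost-effectiveness compared with usual care (Wait-list control [WLC]) for primary dysmenorrhea treatment". *Scientific premises for the study hypotheses* repeats it.

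The analysis under *Statistical tests and anticipated results*, Hypothesis 3, fits that hypothesis. Seemingly unrelated regression (SUR) estimates the cost difference ΔC and the effect difference ΔE jointly. On effects, "The EQ-5D responses will be converted into utility scores to estimate the gain or loss of quality-adjusted life-years". Then "The incremental cost-effectiveness ratio (ICER) will be calculated using the formula ICER = ΔC / ΔE", with bootstrap uncertainty, a cost-effectiveness plane and an acceptability curve (CEAC). Of the threshold λ the protocol says that "the amount of money the country is willing to pay to gain one unit of effect (QALY) will be calculated". It names two further thresholds for checking robustness: GDP per capita and a set of published country-specific values.

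The last sentence of the same section sets the criterion: "Hypothesis 3 will be supported if HIAT yields cost (direct and indirect) savings and results in lower healthcare utility compared with WLC", assessed at T2.

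The *Economic evaluation* paragraph makes the 12-week comparison at T2 from a societal perspective the primary one, and counts the cost of the intervention in both the societal and the healthcare perspective. Under *Intervention*, "the participant-to-research person ratio will be 1:1".

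**The concern.** Cost-effectiveness relates what is spent to what is gained. The criterion looks only at spending and resource use. It has no QALY, ICER, threshold or CEAC term, although all of these are to be estimated a few lines earlier. The phrase *healthcare utility* is also undefined: the section uses *utility* for EQ-5D scores and *utilisation* for services and medication.

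At stake is the declared verdict on one of three study hypotheses, which *Scientific premises for the study hypotheses* says should help decision-making in Hong Kong. A report that follows the protocol could have to call Hypothesis 3 unsupported while its own ICER and CEAC favour HIAT, or the reverse. This is not detail left for an analysis plan, because the protocol itself fixes the rule.

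**Working it through.** **Nothing to reproduce.** The protocol gives no λ, cost, QALY or power figure for Hypothesis 3. The check compares its decision rule with its own ICER framework.

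**Step 1: the rule against ICER = ΔC/ΔE.** For a QALY gain (ΔE > 0), an ICER below λ is the same as positive incremental net monetary benefit, NMB = λ × ΔE − ΔC > 0. The NMB form also handles a QALY loss. With *utility* read as *utilisation*:

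| Result | Cost-effective? | Protocol's rule |
|---|---|---|
| ΔC > 0, ΔE > 0, ICER < λ | Yes | Always fails: no saving |
| ΔC > 0, ΔE > 0, ICER > λ | No | Fails |
| ΔC < 0, ΔE > 0 | Yes | Passes only if utilisation also falls |
| ΔC < 0, ΔE < 0, saving too small for the loss | No | Passes if utilisation falls |
| ΔC < 0, ΔE < 0, saving large enough | Yes | Passes if utilisation falls |
| ΔC > 0, ΔE < 0 | No | Fails |

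Row 1 is always misjudged. Row 4 can be misjudged. Row 3 can be, if savings come through absenteeism while utilisation rises. None of this depends on any assumed number.

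**Step 2: illustration.** All inputs here are assumptions: λ = HK$200,000 per QALY and a utility difference of ±0.05 held for 12 weeks. ΔQALY = ±0.05 × 12/52 = ±0.0115.

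- HIAT better and HK$1,000 dearer: ICER = 1,000/0.01154 = HK$86,667 per QALY; NMB = 2,308 − 1,000 = +HK$1,308. Cost-effective, but the rule fails it.
- HIAT worse and HK$500 cheaper: NMB = −2,308 + 500 = −HK$1,808. Not cost-effective, but it meets the savings condition and passes if utilisation is lower.

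The largest extra cost per participant at which HIAT would still be cost-effective is λ × Δutility × 12/52:

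| Assumed utility gain | ΔQALY | λ = HK$100,000 | λ = HK$200,000 | λ = HK$400,000 |
|---|---|---|---|---|
| 0.02 | 0.0046 | HK$462 | HK$923 | HK$1,846 |
| 0.05 | 0.0115 | HK$1,154 | HK$2,308 | HK$4,615 |
| 0.10 | 0.0231 | HK$2,308 | HK$4,615 | HK$9,231 |

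Any extra cost between zero and the tabulated figure is cost-effective and is failed by the rule.

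**Step 3: is row 1 realistic?** From *Intervention*: 3 sessions a week × 12 weeks = 36 sessions. Each lasts 10 + 30 + 10 = 50 minutes, so 36 × 50/60 = 30 hours of one-to-one supervision per participant (36 × 30/60 = 18 hours if only the training block is counted). The waiting-list arm has none before T2. To pass, HIAT must recover that whole cost within 12 weeks. A QALY gain at positive net cost is therefore plausible. How likely it is cannot be said, because no unit costs are given for supervision, care, medication or absenteeism.

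**The case against.** The best defence is that the protocol does commit to a threshold-based assessment. The further thresholds are there to establish whether HIAT is cost-effective and how robust that conclusion is, and the CEAC is to identify cost-effective options across λ. On this view only the label *supported* is at risk. Part of this stands: the analyses are planned, and ΔC, ΔE, the ICER and the CEAC are unaffected. It does not repair the rule, because the sentence that decides the hypothesis still uses none of them.

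A reader might infer more than the documents support:

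- *That the rule rewards worse health.* This follows only if *healthcare utility* means EQ-5D utility. The same section speaks of healthcare utilisation costs, so a wording slip is the likelier explanation.
- *That costs are counted twice.* The two conditions are joined by *and*; nothing is summed. They overlap, but total cost can fall through absenteeism while utilisation rises.
- *That λ is to be derived from trial data.* The protocol says it will be calculated without saying from what, and it names two external thresholds. A numerical λ may properly be set in the analysis plan.
- *That the verdict turns almost wholly on intervention cost.* The 30 hours are documented, but productivity savings also count in the societal perspective and their size is unknown.

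**Conclusion.** The criterion for Hypothesis 3 is wrong as written. It leaves out the effect side and conflicts with both the stated hypothesis and the planned analysis. It misjudges every result with a QALY gain at extra cost and an ICER below λ, and it can accept a cheaper, lower-utilisation programme that loses QALYs and is not cost-effective.

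This conclusion follows from the protocol's ICER formula and from reading *utility* as *utilisation*. The HK$ figures only illustrate scale and rest on assumed λ, utility and cost differences. The fault is confined to the declared verdict on this hypothesis: Hypotheses 1 and 2, data collection and the economic estimates are untouched.

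**What to change.** Replace the closing sentence so that Hypothesis 3 is supported if, at T2 and from the societal perspective, the incremental net monetary benefit (λ × ΔQALY − ΔC, from the planned SUR and bootstrap) is positive at one primary λ, with the CEAC probability of cost-effectiveness at that λ reported beside it.

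Take λ from an external source and name it before unblinding. One of the two thresholds already cited could serve, with the other kept as sensitivity. It is best named before the coded data are analysed, since *Randomisation and blinding* reveals the group code only after the analyses are complete.

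Report cost savings and resource use as descriptive results, and replace *healthcare utility* with *healthcare utilisation*.

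A stricter bar, such as a bootstrap 95% lower limit above zero, is a choice open to the sponsor. It is not needed to cure this defect, and the sample size was set for Hypotheses 1 and 2 only.

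The cost is a few sentences and a commitment to one threshold in advance. No new data are needed, and the estimates of ΔC, ΔE, the ICER and the CEAC do not change.
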